### Participant-level measures

Eligible participants will complete assessments administered by a member of the research team at baseline, within 1-week post-intervention, and 5 weeks post-intervention. These assessments include the following measures that will be evaluated for their suitability as participant effectiveness outcomes in a definitive trial. We used existing Spanish translations when available. For measures that required translation, we had a bilingual member of our team with experience working with the target population prepare the initial translation, which were then reviewed and piloted to ensure their comprehensibility in the local context:*Psychosocial wellbeing* will be measured using the 9-item Personal Wellbeing Index (PWI) [30]. The personal wellbeing index includes several subscales. Most relevant to this study are the community connectedness and sense of safety subscales. The Spanish version of the full PWI has been validated in Spain where it displayed adequate internal construct validity and excellent internal consistency (α = 0.88) [31]. While no validation studies of the adult PWI have been conducted in Latin America, the adolescent version has been found to display good psychometric properties [32]. Furthermore, an assessment of the PWI’s performance in a multi-country study found evidence of configural measurement invariance and partial metric and scalar invariance across 26 countries [33]. The PWI has also demonstrated good internal consistency among refugee and migrant populations (α = 0.83) [34].*Psychological distress* will be measured using the 6-item Kessler-6 [35]. The Kessler-6 has been used as a measure of psychological distress in Panamá and Ecuador, including during the COVID-19 pandemic [36, 37]. Although it has not been validated specifically in Ecuador or Panamá, it has demonstrated good psychometric properties in Latin America as well as in refugee and migrant populations [34].*Coping* will be measured using the 28-item Brief COPE [38]. The Spanish Brief COPE has been used to measure coping in previous studies in Latin America and has been found to be associated with other constructs of interest to this study (e.g., psychological wellbeing, social support) [39, 40]. Psychometric analyses of the Spanish version of the Brief COPE identified a unique factor structure that. For example, Morán and colleagues identified a single factor that includes both the emotional and instrumental support items, a single factor that included the active coping and planning items, and did not identify an acceptance subscale [41].*Social support* will be measured using the 3-item Oslo Social Support Scale (OSS-3) [42]. The Spanish OSS-3 has been applied in Spain [43], but we did not find evidence that it has been previously used in Latin America. It has also been used in research among immigrant and refugee populations and found to correlate with psychological distress [44, 45].*Functional impairment* will be measured using the 12-item World Health Organization Disability Assessment Schedule (WHODAS) [46]. The WHODAS has been previously applied in Ecuador in clinical samples of people with psychiatric and neurological disorders [47, 48]. Validation studies among Ecuadoran populations have reported good internal consistency (α = 0.81) and high convergent validity of the WHODAS when correlated with other measures of disability or mental health problems [47].

### Service-level measures

We will evaluate several service-level outcomes through routine monitoring including participant engagement and retention, safety, and usability.*Participant engagement and retention* will be assessed using routine session monitoring forms completed by the facilitators capturing attendance and notes from each intervention session.*Safety* will be evaluated as the number of adverse events detected by the research team and reported on an ongoing basis to study investigators and institutional review boards throughout the course of the feasibility trial. We will also inquire about safety through semi-structured interviews with facilitators during the process evaluation.*Usability*, which is defined as ‘the extent to which an intervention can be used to achieve specified goals with effectiveness, efficiency, and satisfaction,’ using the 10-item Intervention Usability Scale [49]. The facilitators will complete the Intervention Usability Scale in relation to their experience delivering *Entre Nosotras* after the final session of the intervention. The Intervention Usability Scale was adapted from the commonly used System Usability Scale [50, 51], and has displayed a two-factor structure measuring whether a psychosocial intervention is (1) learnable; and (2) usable [49].

### Implementation-level measures

We will evaluate a range of implementation outcomes pertaining to both the intervention and research procedures.

#### Appropriateness of intervention and research procedures

We will consider the proportion of those screened who are *eligible* and *sensitivity to change* of our study outcome measures as indicators of appropriateness (i.e., how well aligned our eligibility criteria and outcome measure selection are to the profile and needs the target population).We also consider *intervention fidelity* as an indicator of appropriateness. As members of the community trained to deliver this adaptable and flexible intervention, the facilitators may deviate from the manualized intervention to improve the fit of the intervention to the participant’s needs. Intervention fidelity will be evaluated using two methods. A member of our research team will observe at least two sessions and externally assess fidelity using a checklist that indicates whether each activity within a session was completed well, could be improved, or was not implemented. At the end of each session, the facilitator pair reviews the session and for each activity documents whether it was completed and, if so, whether it could be improved; any difficulties they experienced with the activity that may have influenced whether and how it was implemented (e.g., fit/appropriateness); things that worked well (if implemented); or ways in which the activity could be improved.During the process evaluation, facilitators and participants will be asked open-ended questions related to the *appropriateness of the intervention and research procedures*. These questions will be informed by the Johns Hopkins Dissemination and Implementation Science Measure [52].

#### Acceptability of intervention and research procedures

*Acceptability* will be measured by asking participants and facilitators open-ended questions about their satisfaction with the intervention, whether they liked attending or delivering *Entre Nosotras* sessions, and whether the components of the intervention made sense and were useful during the process evaluation interviews. We will also ask about safety as an indicator of poor acceptability.

#### Feasibility of intervention and research procedures

Feasibility of research procedures will include examining the *rate of recruitment*, whether *randomization* produced balanced groups within site, study *attrition*, and *protocol deviations* assessed using routine study monitoring forms.We will examine whether *contamination* occurred using data from the externally-rated fidelity assessments. We will consider any application of Doing What Matters in Times of Stress material in the standard *Entre Nosotras* intervention or the omission of Doing What Matters in Times of Stress material in the enhanced *Entre Nosotras* intervention as evidence of contamination.We will explore the *construct validity, internal consistency, and sensitivity to change* of measures of psychosocial wellbeing, psychological distress, coping, social support, and functioning to determine whether they may serve as suitable outcome measures for the definitive trial.Feasibility of intervention procedures will focus on whether facilitators are able to achieve the competencies necessary to deliver the *Entre Nosotras* intervention. *Facilitator competency* will be assessed by a member of the research team at the end of training and during the sessions that are observed for the fidelity assessments using a subset of items from the Enhancing Assessment of Common Therapeutic factors (ENACT) rating scale. Specifically, we selected six items from the ENACT that are relevant to the non-clinical nature of the *Entre Nosotras* intervention: (1) non-verbal communication and active listening: eye contact, facial expression, body language, and gestures; (2) verbal communication skills: open-ended questions, summarizing, and clarifying statements; 3) rapport building and self-disclosure; (4) exploration, interpretation, and normalization of feelings; (5) demonstration of empathy, warmth, and genuineness; and (6) elicitation of feedback when providing advice, suggestions, and recommendations. These items are measured on a 3-point scale indicating whether the facilitator needs improvement, partially demonstrated this competency, or demonstrated this competency well. Each facilitator in the pair is rated separately by the external rater.During the process evaluation, facilitators will be asked open-ended questions about the *feasibility* of implementing *Entre Nosotras* including general intervention feasibility, *adoptability* within the study contexts, and *potential for scalability and sustainability*. Participants and facilitators will also be asked to identify *barriers and facilitators* to implementation as well as *strategies* for overcoming barriers and leveraging facilitators.

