### Outcomes

This feasibility trial aims to assess the appropriateness, acceptability, feasibility, and safety of implementing and evaluating *Entre Nosotras*, including when integrated with a stress management component, for migrant and host community women in Ecuador and Panamá. These outcomes will determine whether the study should progress to a definitive cluster-randomized comparative effectiveness trial and whether any research design or intervention adaptations are needed. These feasibility trial outcomes will be assessed using indicators and means of verification that are measured at the participant, service, and implementation level [29]. Table 2 details the outcomes, indicators that will determine progression to the definitive trial, means of verification, and assessment time points.

**Table 2 Tab2:** Study outcomes, indicators, and means of verification

Outcome	Indicator(s) for progression to definitive trial	Means of verification	Participants assessed	Time points			
				Screening/baseline	Intervention ***(5 weeks)***	Post-intervention	5-week follow-up
Appropriateness	**Eligibility:** > 50% of persons are screened are eligible	Routine study monitoring forms	Screened individuals	X			
	**Sensitivity to change:** Small to moderate within-group changes in outcome measures (*d* > 0.2)	Brief-COPE, K-6, OSS, PWI, WHODAS	Participants	X		X	X
	**Intervention fidelity:** > 75% fidelity to the intervention elements	Fidelity assessment^a^	Facilitator pairs		X		
	**Stakeholder perspectives:** Participants and facilitators report that the intervention and research procedures are appropriate and relevant to the needs of host and migrant women	Qualitative interviews	Participants, facilitators			X	X
Acceptability	**Intervention engagement and completion:** > 85% of participants attend first session; > 67% participants complete at least 4 sessions	Routine study monitoring forms	Participants		X		
	**Intervention usability:** Facilitators consider the intervention to have above average usability (IUS Score > 68).	Intervention Usability Scale	Facilitators		X		
	**Stakeholder perspectives:** Participants and facilitators report that the intervention and research procedures are acceptable and safe for host and migrant women	Qualitative interviews	Participants, facilitators			X	X
Feasibility	**Recruitment rate:** Average rate of enrollment is 5 women per week, at minimum, in each community	Routine study monitoring forms	Participants	X			

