	**Randomization:** No moderate to large differences (*d* > 0.5; Φ > 0.3) in baseline characteristics between study conditions within study sites	Demographics, Brief-COPE, K-6, OSS, PWI, WHODAS	Participants	X			
	**Attrition:** > 80% of participants complete baseline, post-intervention, and follow-up assessments	Demographics, Brief-COPE, K-6, OSS, PWI, WHODAS	Participants	X		X	X
	**Fidelity to research procedures:** No major protocol deviations	Routine study monitoring forms	Research assistants	X	X	X	X
	**Facilitator competencies:** An average score of > 2 on competency items, suggesting partially-fully demonstrating the competencies during intervention implementation	ENACT^a^	Facilitators		X		
	**Contamination:** Stress management components from the experimental conditions are included in all sessions for groups randomized to the enhanced intervention and none of the sessions for groups randomized to the standard intervention	Fidelity assessment^a^	Facilitator pairs		X		
	**Performance of outcome measures:** All outcome measures display adequate construct validity and internal consistency	Brief-COPE, K-6, OSS, PWI, WHODAS	Participants	X		X	X
	**Stakeholder perspectives:** Participants and facilitators report that the intervention and research procedures are feasible, adoptable, scalable, and sustainable. Participants and facilitators identify barriers and facilitators to implementation as well as strategies for overcoming/leveraging these factors.	Qualitative interviews	Participants, facilitators			X	X
Safety	**Adverse events:** Detected in < 10% of participants; no serious adverse events attributed to study participation	Adverse event reporting	Participants	X	X	X	X
	**Stakeholder perspectives:** Participants and facilitators report that the intervention and research procedures are acceptable and safe for host and migrant women	Qualitative interviews	Participants, facilitators			X	X

*Abbreviations*: *IUS* Intervention Usability Scale, *K-6* Kessler-6, *OSS* Oslo Social Support Scale, *PWI* Personal Wellbeing Index, *WHODAS* World Health Organization Disability Assessment Schedule

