^a^Fidelity assessment includes a self-administered assessment completed by the facilitator pair at the end of each session as well as an external assessment completed by a member of the research team at two or more sessions per group. Six items from the ENACT that were relevant for a non-clinical, group psychosocial intervention (non-verbal communication and active listening; verbal communication; rapport building and self-disclosure; exploration, interpretation and normalization of feelings; demonstration of empathy, warmth, and genuineness; elicitation of feedback when providing advice, suggestions, and recommendations) were selected to assess facilitator competencies during the facilitator training and are also evaluated by a member of the research team at the 2+ sessions during which they administer the external fidelity assessment

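### The contamination rule covers every session, but the text checks it only with external ratings guaranteed at two of five sessions per group, in conflict with Table 2

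*Protocol article*

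**What the plan says.** The Contamination row of Table 2 (Outcomes section) is one of the indicators for progression to the definitive trial. It requires that stress management components "are included in all sessions for groups randomized to the enhanced intervention and none of the sessions for groups randomized to the standard intervention".

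The row names the fidelity assessment as its means of verification and points to footnote a. That footnote describes two parts: a form that each facilitator pair fills in after every session, and an "external assessment completed by a member of the research team at two or more sessions per group".

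The section on appropriateness of intervention and research procedures repeats the external minimum: "A member of our research team will observe at least two sessions and externally assess fidelity using a checklist". It adds that the facilitators' own form records, activity by activity, whether each was carried out.

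The section on feasibility of intervention and research procedures then says that the team will examine whether contamination "occurred using data from the externally-rated fidelity assessments". It does not mention the facilitators' form. The same paragraph sets the threshold: "We will consider any application of Doing What Matters in Times of Stress material in the standard" intervention counts as contamination, and so does leaving that material out of the enhanced intervention.

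**The concern.** A rule stated over all five sessions is to be judged, according to the text, from a source guaranteed at only two of them. Table 2 and its footnote name a wider source that reaches every session. An analyst following the text and one following the table could reach different answers on the same trial.

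The stake is the contrast that the definitive trial is meant to test. The Study design section says that trial will ask whether adding stress management improves outcomes beyond *Entre Nosotras* alone. Whether the arms stayed distinct is therefore one of the main things this feasibility trial has to establish. A finding of no contamination carries little weight if more than half of the sessions were not looked at.

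**Working it through.** **Inputs**
- Sessions per group: 5 (Intervention section).
- Groups: 7 + 7 + 8 = 22 (Table 3). Check: 22 × 10 women = 220, which agrees with the stated sample size.
- Externally rated sessions per group: at least 2 (footnote a; section on appropriateness).
- Not stated: how rated sessions are chosen, how many groups are in the standard arm, and how often contamination might occur. These are assumed below.

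**Coverage at the minimum**
- All sessions: 22 × 5 = 110.
- Externally rated: 22 × 2 = 44 (40%).
- Not rated: 110 − 44 = 66 (60%).

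**Detection within one group**

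Assume the two rated sessions are a random pair and the rater misses nothing. If k of the five sessions are contaminated, P(seen) = 1 − C(5−k, 2)/C(5, 2), with C(5, 2) = 10.
- k = 1: 1 − 6/10 = 0.40
- k = 2: 1 − 3/10 = 0.70
- k = 3: 1 − 1/10 = 0.90
- k = 4 or 5: 1.00

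With three rated sessions the k = 1 figure becomes 0.60, with four 0.80, and with all five 1.00.

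**Detection across the trial**

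If each community has at least two groups, each site keeps at least one standard community, and at least half of each site's communities are enhanced, the standard arm has between 3 + 2 + 2 = 7 and 4 + 3 + 4 = 11 groups (Guayaquil, Tulcán, Panamá City). Let p be the assumed chance that a standard session is contaminated, independently of the others. For G groups, P(any exists) = 1 − (1−p)^(5G) and P(any seen) = 1 − (1−p)^(2G). The chance that the rule passes although contamination exists is 1 − P(seen)/P(exists).

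| p | G = 11: exists | seen | false pass | G = 7: exists | seen | false pass |
|---|---|---|---|---|---|---|
| 1% | 0.43 | 0.20 | 53% | 0.30 | 0.13 | 56% |
| 2% | 0.67 | 0.36 | 47% | 0.51 | 0.25 | 51% |
| 5% | 0.94 | 0.68 | 28% | 0.83 | 0.51 | 39% |
| 10% | 1.00 | 0.90 | 10% | 0.98 | 0.77 | 21% |

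With no contamination seen in 22 rated standard-arm sessions (G = 11), the 95% upper bound on p is 1 − 0.05^(1/22) = 12.7%. With 14 rated sessions (G = 7) it is 1 − 0.05^(1/14) = 19.3%.

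**The case against.** **The table already names an every-session source.** This stands. A reader of the feasibility section alone might infer that the plan ignores the facilitators' form. Table 2 and footnote a show otherwise, so the defect is a disagreement between two places, not the absence of a source.

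**Two is a floor, and repeated contamination would be found.** This also stands. A reader might infer that most contamination would go unseen. That is true of sessions at the minimum and of a single isolated lapse in a group. It is not true of repeated lapses in a group (0.70 to 1.00) or, with 11 standard groups, of the trial-level rule once p is about 5% or more.

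**External raters are the better witnesses.** The Blinding section leaves facilitators unblinded, and they would be reporting on their own departures. Preferring independent ratings is defensible. That is a reason to keep the ratings as a check, but it does not make two sessions enough for a five-session rule.

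**The omission limb.** Counting omission in the enhanced arm as contamination with no tolerance, beside a fidelity indicator of "> 75% fidelity to the intervention elements", might suggest that one lapse fails both. It does not: missing one whole session of five still leaves 80%. Nor does the article show that one skipped exercise stops progression. Table 2 can be read as requiring some stress management material in each session, and the Outcomes and Discussion sections allow procedures to be modified when an indicator shows a problem. Moving omission to the fidelity threshold would also be unsafe. If the Table 1 objectives are taken as the fidelity elements (an assumption), 5 of 16 are stress management, so an enhanced group could omit it in three of five sessions and still score 13/16 = 81%.

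**Conclusion.** The point holds as an internal conflict with a practical consequence. Table 2 with footnote a, and the feasibility section, name different data sources for the same progression indicator. Under the narrower one, an all-or-none rule over 110 sessions may rest on 44. A single contaminated session in a group is then missed with probability 0.60, so isolated contamination can be reported as none.

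These figures assume the minimum number of ratings, rated sessions chosen at random and a perfect rater. The trial-level figures also assume independent sessions, 7 to 11 standard groups and the listed values of p. More ratings would raise detection; facilitators keeping closer to the manual when observed would lower it.

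The conflict should be resolved, but it does not show that the trial would fail to notice widespread contamination.

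**What to change.** In the feasibility section, name both sources from footnote a. Count contamination if either the facilitators' end-of-session form (all five sessions, both arms) or an external rating shows it. Use the externally rated sessions to report how well self-report agrees with observation.

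Make sure the standard-arm form asks whether any Doing What Matters material was used. The article says the form records whether activities were carried out, but not whether it captures added material, and the form itself is not shown.

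Report leakage into the standard arm and omission in the enhanced arm as separate results, since they are different failures. Keep both within the contamination indicator, and do not move omission to the fidelity threshold.

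If only external ratings are kept, restate the criterion as applying to observed sessions and say how those sessions are chosen.

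The cost is a wording change and at most one item on a form already in use. Coverage rises from 44 to 110 sessions, and one contaminated session falls within a covered session with probability 1.00 instead of 0.40. Coverage is not proof of detection: the added sessions rest on self-report by unblinded facilitators, who may under-report.

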
### Sample size

At least two groups (range 2–4) will be implemented per study community. We aim to enroll up to 220 women (10 women per group). A summary of the target sample size (participants, groups) by study site and community is provided in Table 3. This sample size is comparable to prior feasibility trials of group psychosocial interventions and will enable us to sufficiently pilot the study procedures and evaluate the relevance, acceptability, and feasibility of the intervention and trial design [53, 54]. A sample size of 220, is expected to provide sufficient power to evaluate the construct validity and internal consistency of the study outcome measures in a confirmatory factor analysis under most scenarios (e.g., number of parameters and magnitude of loadings) [55].

**Table 3 Tab3:** Sample size by site and community

Site	Communities (***unit of randomization)***	Number of groups	Number of participants
Guayaquil, Ecuador	• La Florida • Mapasingue and Martha de Roldós	7	70
Tulcán, Ecuador	• Julio Andrade • San Pedro de Huaca • Santa Martha de Cuba and San Luis	7	70
Panamá City, Panamá	• Arraijan • La Chorrera • Panamá City • San Miguelito	8	80

